# The Hip Fracture Surgery in Elderly Patients (HIPELD) study: protocol for a randomized, multicenter controlled trial evaluating the effect of xenon on postoperative delirium in older patients undergoing hip fracture surgery

**DOI:** 10.1186/1745-6215-13-180

**Published:** 2012-09-27

**Keywords:** Hip fracture, Postoperative delirium, Xenon

## Abstract

**Background:**

Strategies to protect the brain from postoperative delirium (POD) after hip fracture are urgently needed. The development of delirium often is associated with the loss of independence, poor functional recovery, and increased morbidity, as well as increases in length of hospital stay, discharges to nursing facilities, and healthcare costs. We hypothesize that xenon may reduce the burden of POD, (i) by avoiding the need to provide anesthesia with a drug that targets the γ-amino-butyric acid (GABA)_A_ receptor and (ii) through beneficial anesthetic and organ-protective effects.

**Methods and design:**

An international, multicenter, phase 2, prospective, randomized, blinded, parallel group and controlled trial to evaluate the incidence of POD, diagnosed with the Confusion Assessment Method (CAM), in older patients undergoing hip fracture surgery under general anesthesia with xenon or sevoflurane, for a period of 4 days post surgery (primary outcome) is planned. Secondary objectives are to compare the incidence of POD between xenon and sevoflurane, to evaluate the incidence of POD from day 5 post surgery until discharge from hospital, to determine the time to first POD diagnosis, to evaluate the duration of POD, to evaluate the evolution of the physiological status of the patients in the postoperative period, to evaluate the recovery parameters, to collect preliminary data to evaluate the economical impact of POD in the postoperative period and to collect safety data. Patients are eligible if they are older aged (≥ 75 years) and assigned to a planned hip fracture surgery within 48 h after the hip fracture. Furthermore, patients need to be willing and able to complete the requirements of this study including the signature of the written informed consent. A total of 256 randomized patients in the 10 participating centers will be recruited, that is, 128 randomized patients in each of the 2 study groups (receiving either xenon or sevoflurane).

**Trial registration:**

EudraCT Identifier: 2009-017153-35; ClinicalTrials.gov Identifier: NCT01199276

## Background

Postoperative delirium (POD) is an acute confusional state associated with changes in consciousness, arousal level and cognitive status characterized by inattention within 30 days after an operation 
[1] and occurs in 15 to 53% of older patients 
[1,2] particularly in those with hip fractures 
[1,3]. We have recently conducted a meta-analysis showing that delirium associated with hip fracture doubles the hazard ratio of death (HR 2.3 95% CI 1.4 to 3.9) 
[1]. Furthermore the development of delirium often initiates a cascade of events culminating in the loss of independence, poor functional recovery, and increased morbidity, as well as increases in length of hospital stay, discharges to nursing facilities, and healthcare costs 
[1-6].

The pathogenesis of delirium is poorly understood though Sanders has proposed that delirium can be considered as a ‘cognitive disintegration’ whereby the integrated neural function of the brain is broken down producing a varied range of symptoms focused on consciousness, arousal and memory 
[7]. Within the proposed framework various non-modifiable patient risk factors are hypothesized to contribute to reduced network connectivity (a surrogate for integration) at baseline, for example, age 
[7]. Modifiable risk factors (including inflammation and sedative drugs) act to further decrease network integration in the brain through altering the balance of neural transmission predominantly through increases in inhibitory tone mediated by γ-amino-butyric acid (GABA) signaling in the brain 
[7]. A prediction of this theory is that avoidance of GABAergic drugs, that include the majority of anesthetic (for example, sevoflurane or propofol) and sedative agents, would reduce the burden of postoperative and intensive care delirium.

In parallel, research showing multiple beneficial effects of the non-GABAergic anesthetic agent xenon has been published. As an inert, noble gas, xenon is not metabolized by the body but yet exerts myriad biological effects, the most notable being anesthesia and organ protection 
[8-18]. Xenon is thought to produce anesthesia through targeting either excitatory *N*-methyl-d-aspartate or two-pore-domain-potassium channels but not GABA_A_ receptors 
[8,9,13]. Xenon anesthesia is rapid onset, cadiostable and xenon is not thought to disturb autoregulation of organ blood flow 
[8,9,13]. Furthermore, xenon protects the brain, heart and kidney from diverse toxic insults including ischemia 
[8,9,13,18]. Xenon exerts a diverse array of neuroprotective effects (for example, induction of B-cell lymphoma-extra large (Bcl-xl), phosphorylated cAMP response element binding protein (pCREB) and hypoxia-inducible factor (HIF)-1α cell survival proteins) 
[11,12,18] and importantly synergizes with other neuroprotective strategies (for example, hypothermia and α2 agonists) 
[10,11,19].

We therefore hypothesize that xenon may reduce the burden of POD (i) by avoiding the need to provide anesthesia with a drug that targets the GABA_A_ receptor and (ii) through beneficial anesthetic and organ-protective effects. Based on our hypotheses we designed a multicenter European randomized controlled trial comparing xenon with sevoflurane anesthesia.

Our working hypotheses are: (1) xenon may contribute to a lower incidence of POD as compared to sevoflurane, within 4 days post surgery; (2) xenon may contribute to reduce postoperative organ dysfunction; and (3) xenon may reduce healthcare costs associated with POD.

## Methods and design

The design of the study was approved by the clinical ethical review committee (Clinical Ethical Review Committee; Medical Faculty; RWTH Aachen; EK 050/10) and by the local ethical review committees of the participating centers and by the competent authorities of the five participating countries prior to patient recruitment.

### Methodology

This phase 2 study is an international, multicenter, prospective, randomized, blinded, parallel group and controlled trial.

### Objectives

The primary objective of this study is to evaluate the incidence of POD, diagnosed with the Confusion Assessment Method (CAM; see 
Additional file 1) 
[20], in older patients undergoing hip fracture surgery under general anesthesia with xenon or sevoflurane, for a period of 4 days post surgery. The secondary objectives of this study are: to evaluate the incidence of POD from day 5 post surgery until discharge from hospital; to determine the time to first POD diagnosis; to evaluate the duration of POD; to evaluate the evolution of the physiological status of the patients in the postoperative period; to evaluate the recovery parameters; to collect preliminary data to evaluate the economical impact of POD in the postoperative period; and to collect safety data.

### Number of patients

A total of 256 patients will be included in this clinical trial. After having received local ethics committee and national competent authority approvals, patients are being recruited. Each patient who accepts to participate in the study will sign the written informed consent before performing any study specific procedure.

### Inclusion and exclusion criteria

The criteria for inclusion are: older patient (≥ 75 years); patient with planned hip fracture surgery within 48 h after the hip fracture; patient willing and able to complete the requirements of this study, including the signature of the written informed consent.

The criteria for exclusion are: patient suffering from multiple fractures, pelvic fractures proximal, pathological fractures, femur fractures (that is, fractures of the middle or distal femur); disabling neuropsychiatric disorders (severe dementia, Alzheimer’s disease, schizophrenia, depression); brain trauma within 12 months prior to selection, history of stroke with residuals; patient suffering from delirium (CAM diagnosis) at selection; patient who cannot complete the preoperative mental tests (CAM and/or Mini-Mental State Examination (MMSE)) of this clinical trial; patient with MMSE score < 24 at selection; patient known to susceptible to malignant hyperthermia; patient with elevated intracranial pressure; patient with a risk of high oxygen demand; patient with recent (less than 1 month) or ongoing myocardial infarction/damage; patient with severe cardiac failure or patient with severe impaired left ventricular systolic function; patient with known severe lung and/or airway disease, or severe chronic respiratory insufficiency, or a sustained homecare oxygen therapy; contraindication (serious illness or medical conditions) for general anesthesia; known allergy or hypersensitivity to any drugs administered during this clinical trial; previous participation in this clinical trial; participation in another clinical trial within 4 weeks prior to selection, or concurrent treatment with any other experimental drugs; history of alcohol or drug abuse or psychiatric disorders that would impair the understanding of the necessary information or render medically or legally unable to give written informed consent.

### Investigational plan and treatments

Eligible patients will be randomly assigned to one of the two study groups (group A: xenon 60% (55% to 65%; 1 minimal alveolar concentration (MAC)) in oxygen (FiO_2_ = 0.35 to 0.45) or group B: sevoflurane 1.1% to 1.4% (1 MAC) in oxygen (FiO_2_ = 0.35 to 0.45) and medical air). Throughout the study, there will be two teams of physicians involved in the patient’s follow-up (see Figure
1).

**Figure 1 F1:**
[figure not shown]
**Study flow chart of the Hip Fracture Surgery in Elderly Patients (HIPELD) study.** V = visit; d = day; hrs = hours, GA = general anesthesia.

Physician 1 will perform visits 0, 2, 3, 4, 5, 6, 7 and 8, which includes selection of patients, follow-up visits and study end visit. Physician 1 will be kept blinded regarding the natures and doses of all study drugs administered throughout the study (Table
1 and Figure
1).

**Table 1 T1:** Study evaluations

	**Visit 0**^**a**^**(selection)**	**Visit 1**^**b**^ (**GA)**	**Visit 2**^**a**^**(3 h post GA)**	**Visit 3**^**a**^**(day 1)**		**Visit 4**^**a**^ (**day 2)**		**Visit 5**^**a**^ (**day 3)**		**Visit 6**^**a**^ (**day 4)**		**Visit 7**^**a**^ (**day 5 to D)**		**Visit 8**^**a**^ (**study end)**
				**A**	**B**	**A**	**B**	**A**	**B**	**A**	**B**	**A**	**B**	
Signed informed consent	X													
Selection criteria	X													
Demographic data	X													
Vital signs	X	X	X	X		X		X		X		X		
Medical and surgical history	X													
Concomitant diseases	X													
Concomitant medication	X	X	X	X	X	X	X	X	X	X	X	X	X	X
MMSE evaluation	X													
Randomization			X											
General anesthesia			X											
Blood sample	X			X		X		X		X		According to investigator’s judgment		
CAM evaluation	X		X	X	X	X	X	X	X	X	X	X	X	
Pain VAS evaluation	X	X	X	X		X		X		X				
Verbal Rating Scale for Nausea		X	X	X										
SOFA	X			X		X		X		X		According to investigator’s judgment		
Recovery parameters		X												
Adverse events		X	X	X	X	X	X	X	X	X	X	X	X	X

A represents 10:00 am ± 30 minutes; B represents 6:00 pm ± 30 minutes; day 5 to D is post-surgery day 5 until discharge from hospital (or at maximum 28 days post surgery), or withdrawal from the study.

^a^Physician 1; ^b^Physician 2.

CAM = Confusion Assessment Method; GA = general anesthesia; MMSE = Mini-Mental State Examination; SOFA = Sequential Organ Failure Assessment; VAS = visual analog scale.

Physician 2 will perform visit 1, which includes randomization and surgical procedure under general anesthesia.

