### Follow-up visits (visits 2 to 7, physician 1)

All randomized patients will be followed up from 3 h to discharge from the hospital (or at maximum 28 days post surgery), or withdrawal from the study. The 4 days following the surgery, CAM, VAS, SOFA and laboratory results, including platelets count, serum hemoglobin, hematocrit, leucocytes, aspartate aminotransferase (AST), alanine aminotransferase (ALT), γ- glutamyltransferase, total bilirubin, serum creatinine and urea concentrations, troponin I or troponin T, C-reactive protein, serum sodium and potassium and serum glucose concentration will be recorded. From day 5 onwards, SOFA and laboratory results become optional. Vital signs, concomitant medications, adverse events and serious adverse events are obtained in all study visits. Details of the study evaluations performed are presented in Table
1.

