### Evaluation criteria

The primary efficacy criterion is POD diagnosed via CAM at least once within 4 days post surgery.

The secondary efficacy criteria include: (1) POD diagnosed with the CAM from day 5 post surgery to discharge from hospital; (2) SOFA from day 1 to day 4 post surgery; (3) recovery parameters; (4) economic parameters, which are addressed to evaluate the economical impact of POD in the postoperative period from the hospital perspective; (5) safety: adverse events and serious adverse events, and laboratory parameters.

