### Statistical methods

The main analysis of the primary efficacy criterion will correspond to the primary objective of the study which is to evaluate the incidence of POD, diagnosed via CAM, in older patients undergoing hip fracture surgery under general anesthesia with xenon or sevoflurane, for a period of 4 days post-surgery. All data collected will be tabulated descriptively by group on the intention to treat (ITT) dataset (which will be composed of all randomized patients). The number of patients having being diagnosed POD with the CAM at least once throughout their study participation from visit 2 to visit 6 will be calculated in each group, and this number of patients will be divided by the total number of participating patients of the corresponding group. This ratio which represents the rate of POD diagnosed within 4 days post surgery will be compared between both groups, using the Pearson’s *χ*^2^ test and its calculation provided by the FREQ procedure of the current version of the SAS software (SAS, Cary, NC, USA), on the ITT dataset.

Additional analyses of the primary efficacy criterion as time elapsed between the onset of the maintenance period of the general anesthesia and the first POD diagnosis with the CAM post surgery (expressed in full number of started hours) will be tabulated by group, as both quantitative and categorical data, in the subgroup of patients for whom POD is diagnosed at least once within 4 days post surgery. Time to first POD diagnosis with the CAM post surgery will also be described globally by group, on the ITT dataset, using Kaplan-Meier estimates to display the probability of survival and of being diagnosed POD. Survival times will be censored at the time of the patients’ last contact (in the subgroup of patients for whom POD is never diagnosed within their trial participation post surgery) or at the time of the first POD diagnosis with the CAM (in the subgroup of patients for whom POD is diagnosed at least once within their trial participation post surgery). If relevant, times to first POD diagnosis with the CAM post surgery will be compared between both groups with the Log rank test.

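### Patients without POD are censored at last contact, not at the last CAM, so unassessed time counts as POD-free in the time-to-POD analysis

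*Protocol article*

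**What the plan says.** Three parts of the protocol article bear on this.

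- **Schedule of CAM.** The row in Table 1 reads "CAM evaluation X X X X X X X X X X X X". By column, the marks fall at visit 0, visit 2, and slots A and B of each of visits 3 to 7. Visits 1 and 8 are blank. The slots are defined by clock time: "A represents 10:00 am ± 30 minutes; B represents 6:00 pm ± 30 minutes". At visit 8, performed by physician 1, only concomitant medication and adverse events are marked.
- **End of observation.** The visit 7 footnote says "day 5 to D is post-surgery day 5 until discharge from hospital (or at maximum 28 days post surgery), or withdrawal from the study". The Follow-up visits section gives the same end points for follow-up, and the Evaluation criteria list "POD diagnosed with the CAM from day 5 post surgery to discharge from hospital" as a secondary criterion.
- **Analysis.** The primary comparison counts patients with a positive CAM "at least once throughout their study participation from visit 2 to visit 6" and divides by the group total. Time to first POD is described by Kaplan-Meier on all randomized patients, with a log-rank test where relevant. For patients who never have a POD diagnosis, "Survival times will be censored at the time of the patients’ last contact".

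**The concern.** In a time-to-event analysis, a patient should stay in the risk set only while the event could be recorded. Here the event is a positive CAM, so that period ends at the last CAM. Last contact can be later in two ways: it can be visit 8, where no CAM is scheduled, or a follow-up contact after CAMs were missed. In either case the rule treats time when nobody looked for delirium as time known to be free of it.

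What is at stake is the time-to-POD curve in each group and the log-rank comparison. The error has a known direction within a group: risk sets are too large at later event times, so the estimated probability of POD is slightly too low. The article states this rule explicitly, so it is not a detail left to the SAP.

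**Working it through.** **1. The plan's own figures.** Inputs from Sample size calculation: 30% versus 15%, two-sided alpha 0.05, power 0.80.

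- n per group = [1.96 × √(2 × 0.225 × 0.775) + 0.8416 × √(0.30 × 0.70 + 0.15 × 0.85)]² / 0.15² = (1.157 + 0.489)² / 0.0225 ≈ 120.5, so 121.
- With 5% dropout: 121 / 0.95 = 127.4, so 128 per group and 256 in total.

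Both figures reproduce, and neither uses a censoring time.

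**2. What the primary rule uses.** Visits 2 to 6 hold 1 + 4 × 2 = 9 scheduled CAMs. The numerator is patients with at least one positive result and the denominator is the group total. Last contact appears nowhere, so the chi-square rule is unaffected.

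**3. Longest gap between scheduled CAMs, from day 1 on.**

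- 10:00 to 18:00 = 8 h, or 9 h with both ±30 min windows at their extremes.
- 18:00 to 10:00 = 16 h, or 17 h with the windows.

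If every CAM is done and visit 8 coincides with exit (assumed), last contact is at most about 17 h after the last CAM. With one CAM missed just before exit, the bound becomes 8 + 16 = 24 h, or 25 h with the windows. If visit 8 falls after exit, the interval is longer by an amount the article does not give. For an exit between visit 2 (3 h after anesthesia) and the first day-1 slot, the gap depends on the hour of surgery.

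**4. Share of a patient's follow-up.** 17 h / (24 h × days):

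| Days followed | Largest unassessed share |
|---|---|
| 5 (assumed) | 17 / 120 = 14.2% |
| 10 (assumed) | 17 / 240 = 7.1% |
| 28 (stated maximum) | 17 / 672 = 2.5% |

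These are worst cases for one patient, not averages.

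**5. Effect on the estimates.** Suppose that at an event time with d first diagnoses the risk set holds n patients, of whom u are past their last CAM. The rule uses d/n where d/(n − u) is right, so the hazard is understated by the factor 1 − u/n. If u/n is the same in both groups, each group's share of the risk set, and so the log-rank expected count, does not change. A between-group distortion needs the gap to differ by group, and nothing in the article points to that.

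**6. Patients who leave inside the 4-day window.** 0.05 × 256 = 12.8, about 13 in total or 6.4 per group. As the primary rule is written, one of them with no positive CAM counts in the denominator only, that is, as POD-free. For scale, assume that dropouts carry the planned risk at a constant rate over 96 h and that every one has a 17 h gap:

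- Sevoflurane: −ln(0.70) × 17/96 = 0.063, a risk of about 6.1%; × 6.4 ≈ 0.4 patients.
- Xenon: −ln(0.85) × 17/96 = 0.029, a risk of about 2.8%; × 6.4 ≈ 0.2 patients.

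The Discussion says that POD peaks on day 1, so the true rate is not constant. This is an order of magnitude only.

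**The case against.** The strongest reply is that CAM coverage runs to exit. Visits 3 to 6 carry two CAMs a day, and visit 7 continues them to discharge, day 28 or withdrawal. A patient who attends every slot has had a CAM within about 17 h of leaving. The timing of visit 8 is not given, the flow chart is not available, and the Follow-up visits section covers visits 2 to 7 only, so visit 8 may be no more than an administrative close-out. The analysis affected is additional, and its log-rank test is conditional.

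All of this stands, and it limits the size of the problem. It does not make last contact the right censoring time. The more visit 8 is a close-out separate from the CAM schedule, the less reason there is to count time up to it as observed.

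A reader might infer three stronger points that the documents do not support:

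- **That delirium status around exit is never measured.** The visit 7 footnote and the twice-daily slots on days 1 to 4 contradict this. What is absent is a CAM tied to the moment of exit.
- **That the primary endpoint loses a material number of cases.** This would need a large share of dropouts to be delirious and missed. Assuming one third, for example, has no source and exceeds the whole planned 4-day incidence in either group (30% and 15%).
- **That the duration objective is compromised by the blank at visit 8.** An exit CAM would show that an episode persists, not when it ends. The article does not describe the duration analysis, which may be in the SAP.

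**Conclusion.** The censoring rule is wrong in principle and small in effect. Time after the last CAM is counted as POD-free in the Kaplan-Meier estimate and the log-rank test. The excess is at most about 17 h per patient from day 1 onwards, provided that no CAM is missed and that visit 8 coincides with exit. Missed CAMs or a later visit 8 lengthen it. The Discussion says POD occurs mainly in the first four days, so for exits after that the extra time falls where few first diagnoses are expected.

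The sample size and the primary chi-square rule stand as they are. Severity is minor.

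**What to change.** In Statistical methods, for patients without a POD diagnosis, replace last contact with the date and time of the last CAM performed as the censoring time. This is one sentence. It needs only the CAM times the schedule already generates, and it can apply to all patients, including the 121 randomized by July 2012.

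Optionally, for patients leaving within the 4-day window (about 13 of 256), physician 1 could do a CAM at the existing study-end visit. The primary count would then have to name that assessment alongside visits 2 to 6. The cost is a few minutes per patient. A withdrawing patient may decline, and those who left before the change would not have it.

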### Pre-anesthetic assessment (visit 0, physician 1)

Within 48 h before their general anesthesia, cognitive function of each patient will be assessed with the MMSE, the presence of delirium will be diagnosed with the CAM, and the Sequential Organ Failure Assessment (SOFA) score ( 
Additional file 2: Table S1) 
[21,22]and level of pain on a 100-mm visual analog scale (VAS) will be assessed. Moreover, a 12-lead electrocardiogram (ECG) will be performed and a blood sample will be collected to assess laboratory parameters. Premedication for general anesthesia will be avoided before surgery, and no premedication impairing cognitive function will be administered on the day of the surgery. Of note, all investigators have been trained to use the CAM and all other test used in this trial.

